## Abstract

**Background:**

Depression is a commonly occurring disorder linked to diminished role functioning and quality of life. The development of treatments that overcome barriers to accessing treatment remains an important area of clinical research as most people delay or do not receive treatment at an appropriate time. The workplace is an ideal setting to roll-out an intervention, particularly given the substantial psychological benefits associated with remaining in the workforce. Mobile health (mhealth) interventions utilising smartphone applications (apps) offer novel solutions to disseminating evidence based programs, however few apps have undergone rigorous testing. The present study aims to evaluate the effectiveness of a smartphone app designed to treat depressive symptoms in workers.

**Methods:**

The present study is a multicentre randomised controlled trial (RCT), comparing the effectiveness of the intervention to that of an attention control. The primary outcome measured will be reduced depressive symptoms at 3 months. Secondary outcomes such as wellbeing and work performance will also be measured. Employees from a range of industries will be recruited via a mixture of targeted social media advertising and Industry partners. Participants will be included if they present with likely current depression at baseline. Following baseline assessment (administered within the app), participants will be randomised to receive one of two versions of the *Headgear* application: 1) Intervention (a 30-day mental health intervention focusing on behavioural activation and mindfulness), or 2) attention control app (mood monitoring for 30 days). Participants will be blinded to their allocation. Analyses will be conducted within an intention to treat framework using mixed modelling.

**Discussion:**

The results of this trial will provide valuable information about the effectiveness of mhealth interventions in the treatment of depressive symptoms in a workplace context.

**Trial registration:**

The current trial is registered with the Australian and New Zealand Clinical Trials Registry (ACTRN12617000547347, Registration date: 19/04/2017).

## Background

Depression is now recognised as one of the leading causes of disability worldwide [1]. As well as being relatively common [2], depression can also be very debilitating [3], with core symptoms inclusive of; an absence of positive affect, persistent low mood, and low activity [4]. Persons with severe depressive symptoms report serious difficulties in all aspects of their life, including work, home, and social activities [5]. In response to the increased identification and recognition of depression [6], there has been greater emphasis on the development of innovative and effective psychological treatments.

The treatment of depression, both pharmacologically and with non-pharmacological interventions, remains a critical area of ongoing clinical research. There is substantial evidence supporting the efficacy of psychotherapy in the treatment of both sub-clinical [7] and clinical levels of depression [8]. Whilst cognitive behaviour therapy (CBT) remains the most empirically supported treatment [9], other therapies such as behavioural activation therapy (BAT) has been shown to be equally effective and also less complex to administer [10]. Service use statistics indicate that despite the effectiveness of such treatments, few people readily access these services [11]. Overcoming identified barriers to accessing psychotherapy such as cost, convenience and accessibility [12] may enhance people’s ability to access evidence based treatments.

Despite experiencing depression many people still remain as active participants in the workforce [13]. Ongoing employment is associated with numerous individual benefits such as economic, psychosocial, and emotional wellbeing [14]. Given its immediacy and core role in the lives of individuals, the workplace may be an avenue for providing psychological interventions to those who might not otherwise access mental health services in a conventional manner [15]. Interventions implemented in the workplace have been found to be effective in improving both mental health and occupational outcomes [16]. This highlights an added benefit of workplace interventions as medical interventions in isolation have not shown as positive an effect on work-related outcomes when compared to workplace interventions [17]. To date, most workplace interventions face accessibility and scalability issues, thus limiting the opportunity for employees to access these services. This issue appears to be particularly prevalent in workers employed in industries where roles are mobile and/or isolated; work hours are often intermittent or excessive; and tasks may be repetitive and high-risk (e.g. such as construction, transport and mining). These industries tend to be male-dominated (males > 70% of workforce) [18] and are associated with higher rates of mental health concerns [18]. Technological innovations, namely smartphones, provide an opportunity for individuals in such roles to learn how to manage their wellbeing and seek further support if required [19].

Mobile health (mhealth) technologies are increasingly being recognised as an effective means through which mental health interventions can be disseminated in the population [20, 21]. Such interventions overcome numerous barriers associated with treatment seeking, including stigma, cost, and accessibility [20]. Encouragingly, there is preliminary support that mhealth interventions can effectively treat symptoms in adults with depression [22]. Moreover, mhealth interventions offer the opportunity for an autonomous, user-directed approach that motivates and offers personalised support by allowing the delivery of content to be tailored to an individual’s interests and needs [23]. This may be particularly advantageous to workplace contexts where, individualised interventions are associated with more consistent outcomes than organisational wide interventions [24]. However, of the many mhealth interventions available on the market, few have been trialled [20] and even fewer have been specifically tailored to a workplace setting.

The proposed HeadGear trial aims to evaluate the effectiveness of a new smartphone app in treating depressive symptoms in a workplace context.

## Methods

### Design

The aim of the current study will be achieved through a multicentre randomized controlled trial, with two parallel arms. The trial will compare two smartphone app-based interventions: a novel intervention app designed for the treatment of depression (Headgear) and an attention control app (mood monitoring). Assessments will occur at baseline, post-intervention (5-weeks), and at 3-month follow-up. The study is registered with the Australian New Zealand Clinical Trials Registry (ACTRN12617000547347) and has ethical approval from the University of New South Wales (UNSW) Human Research Ethics Committee (HC17021). Consent to participate in the trial will be obtained electronically from all participants. The study will be conducted in accordance with the Helsinki Declaration [25] and is compliant with the CONSORT guidelines [26].

### Setting and participants

The study will recruit Australians who are currently employed, and will sample more selectively from a range of male-dominated industries [27]. In Australia, these industries include agriculture/forestry/fishing, utility services (electricity, gas, water and waste), wholesale trade, manufacturing, transport/postal/warehousing, mining, and construction [28]. Emergency services and defence also fit this definition, but were not considered unique industries by the ABS, though for this study they will also be considered as male-dominated.

Industry partner organisations will assist with recruitment by promoting the study among specific groups or their entire workforce. We will aim to recruit at least 850 employed adults across Australia. Organisations that elected to participate will promote the study via their respective health and wellbeing officers, along with email and newsletter advertisements. The study will also be promoted via members of the research team presenting at partner worksites. Social media advertising targeted at employed people will also be utilised to recruit individuals employed externally of partner organisations using an evidence-informed advertising approach [29]. Both males and females will be recruited.

### Eligibility criteria

Initial eligibility criteria are: having a valid telephone number, ownership of an Apple/Android-operating smartphone, fluent in English and living in Australia. As this trial is focused on the treatment of depression, participants will also be excluded from this trial (although still permitted to use the app) if they do not have substantial levels of depressive symptoms at baseline, as indicated by either a PHQ-9 score below 15, or the PHQ-9’s algorithm for a diagnosis for Major Depressive Disorder (MDD) not being met [30]. Participants were excluded if they were under 18 or not currently employed. No exclusion criteria were in place regarding comorbidities or medication use.

### Interventions

#### Active intervention: HeadGear

The intervention condition, *HeadGear*, is a smartphone application-based intervention utilising Behavioural Activation Therapy (BAT) and mindfulness-based therapies. Behavioural Action is a therapy based on learning theory that reconnects people to an environment of positive reinforcement, incorporating elements of value driven action and goal setting [31, 32]. When delivered face-to-face, BAT has been shown to perform as well as CBT for the treatment of depression [33] and preliminary evidence that this translates in mhealth form [34]. The other component utilised in Headgear, Mindfulness, draws on meditation practices to allow individuals to gain further insight into their emotional, physical, and/or cognitive experience to ultimately shape it [35]. Mindfulness has been identified as a transtherapeutic process that targets transdiagnostic mental processes [36], as evidenced by its effect in treating a range of psychopathologies including but not limited to mood, anxiety and substance use disorders [37, 38].

The therapeutic component of *HeadGear* encourages the user to complete one ‘challenge’ each day (5–10 min per day), over 30 days. These ‘challenges’ incorporate a variety of evidence-based BAT and mindfulness techniques and skills, including psychoeducational videos, value-driven activity planning and goal-setting, practice exercises, and techniques for developing coping and resilience (e.g., problem solving, improving sleep, minimising alcohol use, and/or assertiveness training). Other components of the Headgear intervention app include mood monitoring, a skill ‘toolbox’ (progressively built as the skills are completed), and a technical service helpline. Steps have been taken to promote user motivation and engagement by incorporating a ‘daily challenge’ framework where the user is ‘rewarded’ (through skill tokens) upon completing each daily challenge. A challenge framework has been shown to increase the general appeal of an app [39–41]. In addition to these elements, the Headgear application has been designed using participatory approaches and iterative human-computer interaction design strategies [42, 43].

#### Attention-matched control

The attention-matched control condition is a smartphone application that will have the same name and a virtually identical look and ‘feel’ as the intervention version of *Headgear and is* accessed in the same manner*.* However, there is no skill development and no component of behavioural activation or mindfulness therapy. To control for the attentional component of the *HeadGear* application, the control condition will encourage users to use the inbuilt mood monitor daily over a 30-day period and users will also have access to the ‘risk calculator.’

#### Procedure

All interested users will be directed to their respective app store (iTunes or Google Play) directly via a dedicated website (headgear.org.au) where participants register and provide their phone number. Informed consent will be sought digitally via both the website and the app itself. This provides information around the study aims, risks and benefits, confidentiality and dissemination of results. After consent and app download participants will undergo initial screening. Participants who meet the inclusion criteria will then be randomised to receive either the full *HeadGear* app or the attention-matched control version of the app. Participants will be blinded to their allocation. All participants will be provided with appropriate referral information to health services and crisis lines and will be encouraged to seek help from their GP (if this has not already occurred) while completing the trial. The flow of participants through the study phases is shown in Fig.1.

**Fig. 1 Fig1:**
[figure not shown]
Flow of participants through the trial

### Random allocation

Randomisation will occur immediately following completion of the baseline assessment using automated procedures integrated into the trial management software. The algorithm for randomisation will consist of a block design, stratified by industry type, with a block size of 10.

### Assessment

#### Administration of assessments

Assessments will be completed at baseline, post-intervention (5-weeks), and 3-month follow-up. Baseline assessment includes outcome measures pertaining to depression symptomatology (Patient Health Questionnaire (PHQ-9) [44]), wellbeing (World Health Organisation-5 (WHO-5) Well-Being Index [45, 46]), anxiety symptomatology (General Anxiety Disorder-2 item (GAD-2) [47], resilience (Connor-Davidson Resilience Scale 10-item (CD-RISC10) [48]), work performance and absenteeism (Health and Work Performance Questionnaire (HPQ) [49]). In addition to these measures, demographic and service use information will be collected. The application monitors usage data including number of log-ins, frequency of use, time spent in-app, and activity completion rates. This data will be used to examine program engagement.

Post-intervention assessment will occur at 5 weeks’ post-baseline, to allow users extra time to complete the 30-day program. Participants will be reminded to complete the post-intervention assessment via text messages to phone numbers provided in order to address for the possibility that users may delete the app during the trial. Participants will complete an online questionnaire similar to the baseline measure (see Table 1), and again at 3 months post-baseline (“3-month follow-up”). Participants will receive up to three text messages and a call at each follow-up assessment time point, linking them to an online platform through which they can complete the assessment. On completion of each assessment, participants will be entered into a draw to win one of four $200 Visa gift cards.

**Table 1 Tab1:** Assessment measures

	Baseline	Post-intervention	3-month follow-up
Demographics	×		
Patient Health Questionnaire-9 item (PHQ-9) [44]	×	×	×
General Anxiety Disorder-2 item (GAD-2) [47]	×	×	×
World Health Organisation-5 (WHO-5) Well-Being Index [45, 46]	×	×	×
Connor-Davidson Resilience Scale 10-item (CD-RISC10) [48]	×	×	×
Health and Work Performance Questionnaire (HPQ) [49]	×	×	×
Service utilisation and management items	×	×	×
Program feedback		×	

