#### Sample size

As a treatment, the size of the effect of the intervention is anticipated to be moderate. Meta-analysis of previous trials of internet and mobile based treatment of depression showed a large effect size of g = − 0.90 [22]; however unguided interventions typically show smaller effect sizes. Power calculations were carried out using the R package simR [58]. Power was set at 80%, alpha at 0.05, 2-tailed tests, and a correlation of .50 between pre- and post- intervention scores was assumed. Based on these calculations, a sample size of 266 per group was needed (total *N* = 532). A conservative dropout rate of 40% at follow-up was estimated. An initial sample of 851 will therefore be recruited for the trial.

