The proposed trial does carry with it a number of limitations. The use of a smartphone app as a delivery modality does mean that the intervention is unguided and that the user is responsible for managing their interaction with the program. Thus, trial attrition and disengagement are expected issues [64, 65]. It is worth noting, however, that this has also been an issue for face-to-face psychotherapy trials [66]. The reason for drop out in both mhealth and face-to-face trials is often multi-faceted, and whilst can be related to engagement with the program, it is rarely only due to dissatisfaction [67].To account for potential drop out, two procedures were put into place. Firstly, all follow-up communication would occur via phone numbers to ensure that if the participant uninstalled the app before the follow-up period, the participant could still be reached. Secondly, conservative drop-out estimation and the use of statistical methods robust to data missing at random, it is believed that this limitation will be minimised.

Another limitation of the present trial is related to the reliance on self-reported depressive symptoms, rather than a diagnosis of depression achieved through a structured diagnostic interview. This is a common issue faced by most similar trials given the constraints around time and resources. To overcome this issue, we will use a well-validated measure (PHQ-9) that contains two methods for classifying depression: 1) threshold total score above 14 (sensitivity = 67%; specificity = 95%) [68] or 2) meeting the depression algorithm’s criteria (sensitivity = 0.53; specificity = 0.94) [69]. By using both methods, we are confident that participants without significant symptomatology will be excluded and those with significant symptomatology will be included.

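### The follow-up procedure describes no PHQ-9-only fallback for people who do not respond, although 40% loss is expected; a short form at the last 3-month contact would be a cheap improvement of unknown size

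*Protocol article*

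**What the plan says.** Under Administration of assessments, the procedure at 5 weeks and again at 3 months is: "Participants will receive up to three text messages and a call at each follow-up assessment time point, linking them to an online platform". On the content of what is linked, the same section says: "Participants will complete an online questionnaire similar to the baseline measure", with a reference to Table 1. That table marks six blocks at 3 months: PHQ-9, GAD-2, WHO-5, CD-RISC10, HPQ, and the service-use and management items. Entry to the gift-card draw follows completion of an assessment.

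The primary outcome is the PHQ-9 at 3 months. On loss, the Sample size section says: "A conservative dropout rate of 40% at follow-up was estimated". The Discussion adds that "trial attrition and disengagement are expected issues" and names the answers: contact through phone numbers, so that people who uninstall the app can still be reached; a dropout allowance; and an analysis that tolerates data missing at random.

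The article mentions no shorter form and no collection of the PHQ-9 by telephone. It does not say whether partly completed questionnaires are kept, in what order the scales appear on screen, or whether the call follows the texts.

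**The concern.** Of the stated answers to dropout, phone contact helps to reach people, and the other two accommodate loss once it has happened. None reduces what is asked of a participant who has been reached but will not work through the whole set of scales. The contact schedule is given in some detail (number of texts, call, platform, incentive), and a short version for late responders would naturally stand there.

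At stake is mainly the reliance on missing at random. With about two in five randomised participants lacking the 3-month PHQ-9, the primary estimate depends heavily on an assumption that the data cannot test. The two arms also ask for different daily effort (challenges of 5 to 10 minutes against mood monitoring), so non-response could differ between them. An observed PHQ-9 from someone who would otherwise be silent reduces that dependence directly. Precision is the lesser gain.

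**Working it through.** **Inputs.** From Sample size: 266 per group (532 in total), 40% loss, 851 recruited, two-sided alpha 0.05, power 80%. From the descriptions of the measures: the item counts. The effect size is given only in words ("the size of the effect of the intervention is anticipated to be moderate"), so it has to be back-solved. The share of non-responders who would answer nine items is not in the article; I assume 0% to 20%.

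**1. Length of the 3-month assessment.** PHQ-9 9 + GAD-2 2 + WHO-5 5 + CD-RISC10 10 + HPQ 3 + absence 2 + service use 7 = 38. Counting both parts of each absence question (4 instead of 2) gives 40. The self-management ratings come on top; their number is not stated. The primary outcome needs 9.

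**2. The plan's own recruitment figure.** Dividing by the retained fraction gives 532 / 0.60 = 886.7, so 887. The stated 851 is not reproduced that way; it equals 532 × 1.6 = 851.2, which is the number for 37.5% loss (532 / 0.625 = 851.2).

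**3. Observed and missing at the stated loss.** 851 × 0.60 = 510.6, about 511 observed. 851 × 0.40 = 340.4, about 340 missing. The shortfall against 532 is 532 − 510.6 = 21.4.

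**4. Implied effect.** The plan states that "a sample size of 266 per group was needed". With the usual two-sample formula, d = (1.960 + 0.842) × √(2/266) = 0.243. With baseline adjustment at the assumed correlation of 0.50, the same n corresponds to 0.243 × √0.75 = 0.210. Both give 80% power at 266 per group, so the power figures below are the same under either.

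**5. Effect of recovering part of the 340.** Observed = 510.6 + r × 340.4. Power = Φ(0.243 × √(n/2) − 1.960), with n the number per group.

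| Assumed recovery r | Observed | Power, completer calculation |
|---|---|---|
| 0% | 511 | 78% |
| 2% | 517 | 79% |
| 5% | 528 | 80% (79.7%) |
| 10% | 545 | 81% |
| 20% | 579 | 83% |

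Reaching 532 needs r = 21.4 / 340.4 = 6.3%, or 22 of 340 in whole persons, about 1 in 16. At 5% it is not reached.

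**6. Limit of the power column.** It counts only people with a 3-month score. The planned mixed model for repeated measures also uses 5-week scores, so someone missing at 3 months but seen at 5 weeks is not a complete loss, and the true gain in power is smaller than the table shows.

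**The case against.** The strongest objection is that this rests on silence in a condensed article. The reminder script and the handling of partial responses are details that a full protocol may hold. That stands as a limit: a fallback in an unseen document cannot be excluded. But the article lists its procedures against dropout, and a reduced assessment is not among them.

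Three stronger readings are tempting, and the article supports none of them.

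- A reader might infer that anyone unwilling to finish the full questionnaire yields no primary outcome. That would require partial responses to be discarded, which is not stated. PHQ-9 is also the first scale in Table 1, so someone who stops early may already have given it.
- A reader might infer that the call is always the last resort. The order of texts and call is not given.
- A reader might infer that a short form would bring the trial back to 532. That holds only at about 6.3% recovery or more, and no figure supports any rate. The gap exists because 532 was multiplied by 1.6 and not divided by 0.6. A short form does not correct that, and at 37.5% loss there would be no gap.

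It can also be said that length is not shown to cause the loss. The Discussion describes the reasons for dropout as having many sides, and a person who never opens the link is not helped by a shorter form. That stands, and it is why the size of the benefit is unknown.

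Finally, the change has a real cost. Work performance, sickness absence and wellbeing are named secondary outcomes, and the Discussion presents occupational outcomes as part of what makes the trial distinctive. Some people who would have completed everything will stop after nine items. This argues for confining the short form to the last contact at 3 months.

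**Conclusion.** The point holds as an inexpensive improvement to the design. Nothing in the follow-up procedure is stated wrongly. The article describes a single route to a 38 to 40 item assessment, expects 40% loss, and describes no way for a late responder to give the nine primary-outcome items alone. A short form at the last contact would probably add some observed 3-month PHQ-9 scores and lessen the dependence on missing at random. Over assumed recovery of 2% to 20%, the observed number would rise from about 511 to between 517 and 579, and completer power from about 78% to at most 83%, with less gain in the mixed model. The conclusion assumes that 40% loss occurs as planned, that some non-responders can be reached but are deterred by length, and that the full protocol holds no such fallback. The case does not depend on reaching 532, since each additional observed score helps.

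**What to change.** In Administration of assessments, state that at 3 months the last contact, made only to people who have not answered the earlier reminders, offers a PHQ-9-only version on the same online platform, with the remaining scales optional afterwards. State which contact is the last. State also that any completed PHQ-9 is saved and enters the primary mixed model like any other, and whether a PHQ-9-only response qualifies for the prize draw.

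The cost is one short form on a platform already in use and a few sentences of text, with no added contacts or staff. The downside, some missing secondary-outcome values among people who would have completed everything at that contact, should be acknowledged. Counting PHQ-9-only responses separately would show how many scores the form gained.

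Reconcile the recruitment figure separately: 887 for 40% loss, or 37.5% as the loss that 851 allows for.
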